### Intervention

TWM-E will involve teachers adapting 3 × 40 min English lessons per week over a 6-week period. Movement-based learning will be incorporated during teaching selected curriculum from the NSW K-6 English syllabus. The program delivery will involve the following components: (i) full-day professional learning for teachers, (ii) TWM-E equipment pack, (iii) handbook for teachers with examples on how to incorporate movement-based learning into English lessons, (iv) online and PDF resources with lesson examples developed by the research team, (v) three observations with feedback per school by members of the research team during program implementation, which will also function as a fidelity check, and (vi) weekly newsletter emails providing implementation strategy support (i.e., separate advice and tips per school based on observations by the research team).

Firstly, participating teachers will attend a full-day professional learning workshop conducted at the University and delivered by the research team. The professional learning day will be registered and accredited with the National Educational Standards Authority (NESA [53]; NSW Department of Education, 2017). Teachers will earn professional learning hours towards their teacher accreditation (Highly Accomplished Standards 1.2.3, 2.5.3, 4.1.3, 6.3.3). The purpose of this workshop will be to help teachers familiarize themselves with the process of integrating movement-based learning with appropriate English syllabus content. A training model is useful for the dissemination of key knowledge to be used in the intervention. The mentoring model [54, 55] is underpinned by situated learning theory [56] and contextualizes the theoretical content presented to teachers. A summary of the workshop’s content is presented in Table 1.

**Table 1 Tab1:** Summary of the professional learning workshop

1. Course rationale	• Presentation of current research findings that identify prevalence and issues around physical activity, cognitive performance and the K-6 English curriculum
2. Evidence for TWM-E	• Findings of the feasibility trial and comparison with the previous Thinking while Moving in Maths research project
3. Becoming a TWM-E advocate	• Demonstration and planning learning sessions: explanatory videos created by the research team focusing on the benefits of school-based physical activity, physical activity and cognition, using physical activity during lessons, why English lessons should become active, how to make it work in every school, and the benefits of the TWM-E approach
4. Implementing TWM-E at schools	• Demonstration of TWM-E activities using existing lessons designed by the research team • Teachers will modify their own lessons based on the TWM- E approach • Presentation of challenges of successfully implementing and advocating TWM-E in their schools (i.e., establishment of clear pedagogical expectations, tasks and strategies that teachers will need to address when they are in the school setting, and design of implementation plans)
5. Reporting on TWM-E in schools (post workshop)	• Teachers will be required to introduce the TWM-E pedagogy into their school community and provide evidence of its delivery and impact • Teachers will also use resources developed and discussed during the workshop to model, advocate and support colleagues as they incorporate TWM-E into their teaching practice

The workshop is designed to equip teachers with the necessary skills and motivation to use physical activity as a teaching approach for the development of literacy skills, focusing on the benefits of physical activity on students’ engagement, academic and cognitive performance. Teachers will be familiarized through demonstration with activities and learning experiences and provided with resources to promote physical activity integration across the primary school English curriculum. A key focus will be maintained on the desired English outcomes from the current syllabus, and more specifically on spelling and grammar, which are content areas that benefit from rehearsal to consolidate learning. Activities will be aligned with NSW English syllabus. Example ideas, activities, and a potential lesson sequence can be found in Fig. 2.

**Fig. 2 Fig2:**
[figure not shown]
Example of activities and lesson plans

Following the completion of the professional learning workshop, participating schools will receive a teacher-selected TWM-E equipment pack (e.g., chalk, buckets, whiteboards, drill ladders, basketballs, skipping ropes, lettered beanbags, and lettered flexi domes - value $400 AU). Also, teachers will be given access to a website with online modules and movement-based activity examples (via videos) developed by the research team.

The program will be delivered by the regular classroom teacher during the schools’ timetabled English lessons. Teachers will be encouraged to apply their knowledge from the professional development training to prepare and deliver physically active English lessons. All teachers will be emailed a weekly newsletter offering tips and strategies, and will receive three visits during Weeks 1, 3, and 5 of the program. During Weeks 2, 4, and 6, evaluation with feedback will be provided to the teachers by the research team attending while observing the physically active English lessons.

Considerable concerns have been raised from the public health research sector regarding the design and development of interventions that are not feasible to be adopted and implemented in real world settings [57]. A particular emphasis on school-based physical activity has been placed in the state of NSW, Australia, in which government policy requires public schools to offer 150 min of planned physical activity across the school week [58]. TWM-E has been requested by the NSW Department of Education and has been designed to maximize scalability and sustainability. As recommended in the Consolidated Framework for Implementation Research (CFIR), the intervention will target schools, principals, teachers, and students [59]. A summary of the TWM-E components are presented in Table 2. Several implementation strategies have been designed to support the delivery of the TWM-E program including: i) intervention characteristics, ii) outer setting (i.e., educational authorities), iii) inner setting (i.e., schools), iv) characteristics of teachers, and v) implementation process.

**Table 2 Tab2:** Summary of the TWM-E components

Level	Intervention Component	Dose	Description	Implementation evaluation
Teacher	1) Professional learning workshop	1 × 5 h	1) Course rationale 2) Evidence for TWM-E 3) Becoming a TWM-E advocate 4) Implementing TWM-E at school 5) Reporting on TWM-E in schools	• Teacher post-workshop evaluation questionnaire • Post-program implementation questionnaire (Teacher evaluation of the TWM-E pedagogy)
	2) Session observations	3	The research team will conduct three observations of the TWM-E lessons in weeks 2, 4, and 6 using the evaluation Checklist.	• Evaluations Checklist (Fidelity check) conducted by the research team • Teacher interview questions
	3) Support from the research team	On-going	The research team will be available for the teachers throughout the duration of the presentation. Weekly emails including advice and strategies will be sent during Weeks 1, 3, and 5 of the intervention.	• Post-program implementation questionnaire (Teacher evaluation of the TWM-E pedagogy)
School	4) Dissemination to school staff	1 × 45 min	Teachers will present the TWM-E (e.g., objective and program details) pedagogy during their staff meetings.	• School principals will sign off teachers after the completion of their presentation in MyPL (teachers will receive the full NESA accreditation)
	5) Equipment	Once	Schools will be provided with a TWM-E equipment pack selected by the participating teachers to assist in the delivery of the program (e.g., chalk, buckets, whiteboards, drill ladders, basketballs, skipping ropes, lettered beanbags, and lettered flexi domes - value $AU400).	• Post-program implementation questionnaire (Teacher evaluation of the TWM-E pedagogy)
Student	6) TWM-E lessons	3 / week	TWM-E lessons will be run during curricular English time by the regular school teachers. The TWM-E lessons will last for 40 min.	• Student intervention evaluation • Student interview questions

### Measures

Consenting students will be assessed at two time points using identical measures (baseline and 3-months). Trained research assistants will collect student level assessments, and where possible the same assessors will be used for both time points. Research assistants will be blinded to schools’ allocation to the conditions. More specifically, on-task behavior, followed by the cognitive assessments will be conducted by research staff on the same day at the same time for each time point (i.e., Monday, 9:00 am, baseline and posttest). To avoid participant burden, academic achievement tests will be administered by the classroom teachers on a different day using a standardized data collection protocol given to the teachers by the research team. Students’ demographic information characteristics will be collected at the end of the intervention.

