### Academic outcomes

#### On-task behavior

Time spent on-task during English lessons will be observed using momentary time sampling, reported as a percentage of time, categorized as “on-task” (consisted of “actively engaged” or “passively engaged”), and “off-task” [66]. Active engagement refers to the time a child is actively engaged in an academic activity (e.g., reading, writing, or performing the designated task), rather than passive engagement (i.e., looking at an appropriate target (e.g., the teacher) but not actively engaged in the activity). Off-task behavior is related to behavior not associated with the task (e.g., off-task motor behavior, walking around the class, off-task verbal behavior, chatting, or off-task passive behavior, staring in the class [34, 67]. This observational tool has been adapted from the “Behavior Observation of students in schools” and the “Applied Behavior Analysis for Teachers” [66, 68]. Twelve students (6 boys, 6 girls) will be observed during their English lessons (e.g., 9:00–11:00 am) in 15 s intervals on a rotational basis over a 30-min period in the allocated English time slot. Two lesson observations per school at each time point will be included. Two trained research assistants will observe simultaneously, after receiving a 2-h training focusing on identifying and classifying behavior into the appropriate categories, and a practice trial.

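### The unqualified statement that research assistants are blind to allocation cannot be assured for post-test on-task behaviour, which they code live in the lessons that carry the programme

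*Protocol article*

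**What the plan says.** The Measures section assigns student assessment to research assistants: "Trained research assistants will collect student level assessments, and where possible the same assessors will be used for both time points". It then says "Research assistants will be blinded to schools" with regard to allocation. No outcome and no time point is excepted. The sentence that follows turns to on-task behaviour and then the cognitive tests, done in that order on the same day.

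The On-task behavior section fixes the method: "Time spent on-task during English lessons will be observed using momentary time sampling". Twelve students per lesson "will be observed during their English lessons", in 15-second intervals over 30 minutes, with two lesson observations per school at each time point. The coding is live: "Two trained research assistants will observe simultaneously, after receiving a 2-h training".

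Table 2 puts the programme in the same place: "TWM-E lessons will be run during curricular English time by the regular school teachers". For the achievement test (PAT), Measures says that "academic achievement tests will be administered by the classroom teachers on a different day", following a standardised procedure.

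**The concern.** On-task behaviour is a human judgement made in the room, which makes it the outcome most open to an observer's expectations. An active English lesson with ladders, balls and lettered beanbags looks different from a usual one. If observers can see which arm they are in, the stated blinding is a safeguard that the design does not provide. The trial could then report on-task behaviour as blind-assessed when it was not. This matters because the Background section reports gains in on-task behaviour from both earlier Thinking While Moving studies, and the protocol hypothesises improvement on every measure. Research assistants therefore have a direction to expect.

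**Working it through.** No sample size, power or error rate enters this point, and the plan gives no figure to reproduce. The check sets the relevant statements side by side.

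1. **Who observes.** Research assistants, the same people at both time points where possible (Measures; On-task behavior). Someone who saw a class's usual lesson at baseline is well placed to notice a changed format.
2. **Where.** In the allocated English slot (On-task behavior).
3. **Where the programme runs.** In timetabled English lessons, led by the regular teacher, with visible equipment (Intervention; Table 2). Control schools continue usual practice (Participants).
4. **When.** Delivery is in Term 3. Post-test starts midway through Term 3 and runs to the end of that term (Participants). Nothing holds the observation back until delivery has finished.
5. **What the coding needs.** Walking around the class is given as an example of off-task behaviour, yet in a TWM-E lesson movement is the task. To code an active lesson correctly, the observer has to recognise it as active.
6. **Baseline.** Randomisation follows baseline assessment, so baseline coding is blind by design. The problem is confined to post-test.

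Steps 1 to 5 mean that an observer who meets an active lesson at post-test learns the arm. The article does not say that the observed lessons are active, so it is worth asking how much depends on that.

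- Programme time is 3 × 40 min = 120 min = 2 h per week.
- English takes 25–35% of the school week (Background). Assuming a week of 25 to 30 h, which the article does not state, English takes 0.25 × 25 = 6.25 h to 0.35 × 30 = 10.5 h.
- Active share of English time: 2/10.5 = 19% to 2/6.25 = 32%.
- Five intervention schools with two observed lessons each give 10 lessons. If these fell at random and independently in English time, the chance that none is active is (1 − 0.19)^10 ≈ 0.12 down to (1 − 0.32)^10 ≈ 0.02.

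So even if active lessons are a minority of English time and no one aims for them, at least one intervention lesson would be observed in active form with a chance of about 88% to 98%. This illustration rests on the assumed week and on random timing. It does not predict how many lessons would be affected.

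**Executive function.** The order is lesson observation, then cognitive testing, on the same day. The text speaks of research staff for both and does not say whether they are the same individuals. If they are, knowledge gained in the lesson carries into testing. The tests run on iPads and are scored from accuracy and reaction time, so the opening for bias is in how the session is run, not in the scoring.

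**Achievement test.** The regular teacher delivers the programme, and classroom teachers administer the test. The blinding sentence covers research assistants only, so this is a separate exposure. The stated safeguards are a standardised test, exam conditions and a standardised procedure. Who marks it is not stated.

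**Fidelity visits.** The research team observes intervention lessons in Weeks 2, 4 and 6. The article neither says that these visitors also assess outcomes nor says that they do not.

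**The case against.** The strongest reply is that failure of blinding is not shown to be certain. The observed lessons could all be conventional ones, and the off-task codes fit such lessons well. Two trained observers code together, the outcomes concerned are secondary, and staffing detail is often left to a fuller protocol. Part of this stands: the article supports saying that blinding is not assured, not that it fails in every observed lesson. But the blinding statement is categorical, and nothing in the text restricts observation to conventional lessons. Two observers in the same room see the same lesson, so agreement between them does not restore blinding.

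Several stronger readings are tempting and are not supported:

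- **That the teacher-run PAT contradicts the blinding claim.** It does not. The article discloses teacher administration openly and gives participant burden as the reason.
- **That only intervention teachers are trained.** The Abstract says all teachers receive the workshop, and the timing for wait-list teachers is not given. The PAT point rests only on teachers knowing their arm and delivering the programme.
- **That teachers are asked to prove the programme works through the PAT.** The requirement to "provide evidence of its delivery and impact" is in Table 1 under post-workshop reporting to the school community and is not linked to trial scores.
- **That the same individuals observe lessons and test executive function.** The text leaves this open.
- **That accelerometry is fully protected.** It is less exposed, but teachers help to place, distribute and collect the devices.
- **That the bias is about 10 percentage points.** A 30-min lesson has 30 × 4 = 120 intervals, or 120/12 = 10 per child if one child is sampled per interval, so one miscoded interval moves that child's lesson score by 1/10. This shows how coarse the score is. It says nothing about how often, or in which direction, observers would miscode.

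**Conclusion.** The point holds for one secondary outcome and in conditional form for another. For post-test on-task behaviour, the protocol claims a blinding that its own schedule does not secure. For executive function, the risk exists only if the staff who observed the lesson also run the tests, and automated scoring limits it. PAT administration is a bias risk to declare alongside these, not an inconsistency in the text. The accelerometer-based primary outcome is not at issue here.

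The size of any bias cannot be derived from the documents. The conclusion assumes that some observed intervention lessons are active, which the text allows and the timing makes likely. It would fall away for on-task behaviour if observation were restricted to conventional lessons in both arms and the observers had no other route to learning the arm. The correction should be made, because an unsupported safeguard on a subjective outcome would lead readers to underrate detection bias.

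**What to change.** 1. Replace the general blinding sentence with a statement for each outcome, and claim blinding only where it can hold.
2. Declare post-test on-task observation unblinded and interpret its results accordingly. Alternatively, specify that the observed post-test lessons have the same conventional format in both arms; this keeps blinding possible but measures behaviour outside the active lessons, so the outcome definition should say so.
3. Run the cognitive tests before any lesson observation that day, or with existing staff who did not observe.
4. State that staff who make fidelity visits take no part in outcome assessment.
5. State that the PAT is administered by teachers who know their arm, and have it marked by people who do not.

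The cost is wording, some scheduling constraint and a reallocation of existing staff, together with a less favourable risk-of-bias statement for on-task behaviour. Sample size and the analysis model are unchanged.

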### Physical activity

The primary outcome will be children’s physical activity levels during the school day. Objective measurements of intensity and physical activity levels (i.e., counts per minute) will be obtained using tri-axial wrist-worn accelerometers AX3 (Axivity, York, UK). AX3 accelerometers have been found to be a valid and reliable tool for measuring movements [60] [61].

Accelerometers will be distributed on Monday morning and will be collected Friday afternoon. They will be worn for five consecutive school days from 9:00 am to 3:00 pm. Teachers will be trained to assist their students with placement of the accelerometers. They will distribute and collect the accelerometers daily which will be coded for individual students. Accelerometer data will be downloaded in raw format using OmiGui Software and processed in R software (http://cran.r-project.org/) using the software package GGIR [62]. Data extracted between Monday – Friday (9 am – 3 pm) will be retained for the analysis. Non-wear time will be classified within a 60-min time window if for at least two out of the three axes [63]. Data will be reduced by calculating the average gravity-based acceleration units (g), per 1-s epoch, with daily time spent in moderate-to-vigorous physical activity (MVPA) determined using the sum of epochs averaging above 142 mg [64]. The average minutes spent in MVPA per day and average daily wear time will be computed using data from each participant’s valid days. A valid day will be defined as > 5 school hours on any given day [34], with participants included in the analysis if they wear the monitor for at least 3 days [65].

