### Sample size calculation

Power analysis using procedures appropriate for a cluster RCT study design [51] were conducted to determine the sample size required to detect changes in the primary outcome of accelerometer-determined physical activity counts per minute (CPM). Calculations assumed baseline to post-test correlation scores of *r* = 0.30 and were based on 80% power and alpha level 0.05. Based on the reported physical activity effects (i.e., *SD* change = 200 CPM) after six weeks of the TWM in Maths study pilot study, and a conservative intra-class correlation coefficient (ICC = 0.15), a study sample of *N* = 200 with 8 clusters (i.e., schools) of 25 students would provide adequate power to detect a between group difference of 200 CPM across the school day [34, 52].

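### The primary outcome is named and powered as counts per minute, but the stated accelerometer processing ends in MVPA minutes per day and yields no counts

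*Protocol article*

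**What the plan says.** In the protocol article, Sample size calculation sets out to find the "sample size required to detect changes in the primary outcome of accelerometer-determined physical activity counts per minute (CPM"). The SD and the between-group difference are both 200 CPM. The other inputs are a baseline to post-test correlation of 0.30, an ICC of 0.15, 80% power and alpha 0.05, giving 8 schools of 25 children (N = 200).

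The Physical activity section under Measures uses the same unit: "Objective measurements of intensity and physical activity levels (i.e., counts per minute) will be obtained using tri-axial wrist-worn accelerometers AX3". It then describes the data reduction. Raw AX3 files are processed with GGIR: "Data will be reduced by calculating the average gravity-based acceleration units (g), per 1-s epoch". Daily MVPA time is "determined using the sum of epochs averaging above 142 mg". The per-child summaries follow: "The average minutes spent in MVPA per day and average daily wear time will be computed using data from each participant’s valid days".

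No other section settles the variable. The Abstract, Aims and hypotheses, and Discussion speak only of physical activity or physical activity levels. Statistical analyses refers to primary and secondary outcomes and names no variable. The Abbreviations list gives CPM and MVPA as separate terms.

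**The concern.** An analyst who follows the printed steps reaches average MVPA minutes per day. The variable called primary, on which the trial is powered, does not appear at the end of those steps. Counts per minute describe the overall volume of movement, while MVPA minutes are time above an intensity threshold. The two need not respond alike to three 40-minute active lessons a week.

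Two things are at stake. A reader cannot tell from the article which variable carries the primary test. And the power statement uses a difference and an SD in a unit that the stated processing does not deliver.

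This is a conflict between printed statements, not detail left to a fuller document. The processing is specific about software, epoch, cut-point, valid-day rule and minimum days, and it leads to a different unit from the one named.

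**Working it through.** **Step 1: the statements side by side**

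| Place in the article | Activity variable |
|---|---|
| Sample size calculation | Counts per minute, called the primary outcome |
| Physical activity, opening | Counts per minute, by way of definition |
| Physical activity, data reduction | Acceleration in g per 1-s epoch |
| Physical activity, per-child summary | Average MVPA minutes per day (plus wear time) |
| Statistical analyses | None named |

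Three readings are possible, and each requires a change to the text:
- If CPM is primary, its derivation from the raw data is absent from an otherwise specific description.
- If MVPA minutes are primary, the power paragraph and the opening of Physical activity name the wrong variable.
- If counts loosely means mean acceleration, 200 CPM has no stated equivalent in g or mg, and no school-day mean is listed among the summaries.

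**Step 2: reproduce the plan's own N on the CPM scale**

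Inputs from Sample size calculation: difference 200, SD 200 (labelled SD change), r = 0.30, ICC = 0.15, 25 per school, power 0.80, alpha 0.05. Two-sided testing and 1:1 allocation are assumed.

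Design effect = 1 + (25 − 1) × 0.15 = 4.6.

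Total N = 2 × [2 × (SD/200)² × (1.960 + 0.842)²] × 4.6, where (1.960 + 0.842)² is about 7.85.

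- (a) 200 is the SD at one time point and change scores are analysed. SD = 200 × √(2 × (1 − 0.30)) = 236.6, so N = 202.2, or 8.09 schools. Power at N = 200 is 79.6%.
- (b) 200 is the SD of change. N = 144.4. Power at N = 200 is 90.9% by the normal approximation and 78.4% by a t test on 8 − 2 = 6 degrees of freedom.
- (c) 200 is the SD at one time point with baseline adjustment. SD = 200 × √(1 − 0.30²) = 190.8, so N = 131.4. Power at N = 200 is 93.3% (normal) or 82.0% (t, 6 df).

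Reading (a) with the normal approximation, or (b) with the t distribution, comes close to the stated 80% at N = 200. The arithmetic is therefore not in dispute.

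**Step 3: what the target is without units**

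Under (a) it is 200/236.6 = 0.85 SD of the change score. Under (b) it is 200/200 = 1.0 SD.

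**Step 4: what carries over to MVPA minutes**

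The article gives no SD and no target difference in MVPA minutes or in g, so a sample size in those units cannot be computed. It also does not say that ICC 0.15 or r = 0.30 applies to them. If ICC 0.15 and 25 per school are carried over as an assumption, the smallest difference detectable with 80% power, in SDs of the analysed score, is:

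- 8 schools: (1.960 + 0.842) × √(4 × 4.6/200) = 0.85 SD (normal), or 1.02 SD (t, 6 df)
- 10 schools (the number planned in Abstract and Participants), 250 children: 0.76 SD (normal), or 0.87 SD (t, 8 df)

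Power with 8 schools over an assumed range of true differences:

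| Difference (SD) | Normal | t, 6 df |
|---|---|---|
| 0.3 | 17% | 13% |
| 0.5 | 38% | 29% |
| 0.8 | 75% | 60% |
| 1.0 | 91% | 78% |

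The article does not say where in this range an expected effect on MVPA minutes would fall.

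**The case against.** The strongest reply is that the article names only one primary variable. Both places that give a unit give CPM, and nothing calls MVPA minutes primary. The data are kept in raw form, so counts might be derived by a step that a condensed article leaves out. That stands in part: the printed text does not prove that CPM could never be obtained. But the printed steps go to another unit and stop there, so the text still has to be reconciled.

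A second reply is that power depends on the standardised difference, ICC, correlation and cluster size, so the calculation could be restated without CPM. That also stands. The inputs are not worthless for another variable; they have simply not been justified for one.

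A reader might infer more: that the primary test is wholly undefined and will be picked from several measures once the data are seen. The article does not say that any choice is made after the data are seen. Acceleration in g appears as the step to which the threshold is applied, not as a competing outcome. The error rate for two independent tests, 1 − 0.95² = 9.75%, is therefore not a fair size for this point. It presumes such a choice, and it is an upper bound for two measures taken from the same signal, children and days, which would be correlated.

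**Conclusion.** The point holds as an internal contradiction. Counts per minute are named and powered; MVPA minutes per day are what the described processing computes for each child. The statement of 80% power with N = 200 is reproducible for CPM but unsupported for MVPA minutes.

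A reader might go on to infer that the trial is underpowered. The article does not support that: without an SD and an expected difference for MVPA minutes, power for that variable is unknown, and 10 schools are planned against the 8 in the calculation.

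The size of the point is the range in the working. If the ICC and cluster size carry over, 8 schools suit a difference of about 0.85 SD (normal) to 1.02 SD (t, 6 df), and power falls quickly below that. These figures assume two-sided testing, equal allocation, ICC 0.15 for the variable analysed and 25 analysable children per school. Because the point concerns the single primary test, it should be settled before analysis.

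**What to change.** Name one primary variable and use it in Sample size calculation, Physical activity and Statistical analyses. Either repair is sound:

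- Make it average MVPA minutes per valid school day, or another single measure the described processing yields, and remove counts per minute as the primary outcome.
- Keep counts per minute and state how they are derived from the raw AX3 data.

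Make any other activity measure secondary.

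Then restate the power in the chosen unit, with a difference and SD for that variable. Alternatively, express it as a standardised difference (about 0.85 to 1.0 SD). In either case say whether 200 is the SD of change or of a single measurement, and give the ICC and the baseline to post-test correlation as assumptions for that variable.

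The cost is wording in three sections and one recalculation, with no new data. Participants dates baseline to May to June 2018 and the intervention and post-test to July to September 2018. If the named variable is replaced after data collection began, that is a change of primary outcome and needs a dated, documented justification.
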